**Fig. 2 Fig2:**
[figure not shown]
Analysis of mechanisms

We will employ mediation analysis with two-level MSEM models as explicated by Preacher, Zhang and Zyphur [57] and extended to three-level models by Preacher [57]. We will use a combination of limited information estimation frameworks (focused on sub-portions of the full model) and full information estimation frameworks (focused on the entire three-level model) to strategically answer questions. At level 1, child outcomes at the immediate post test are modeled as a function of the family predictors (see Fig. 2) using baseline measures of outcomes and family mediators as covariates, taking into account the clustering at the higher levels of the model. The follow-up (6-month) measures of the mediators and the outcomes are included within the model in a classic SEM panel model with autoregressive effects, thereby linking the follow-up data to the immediate post-test data. This is an advantage of using MSEM over traditional multi-level modeling. Different centering strategies (e.g., grand mean versus group mean) can be explored to garner various perspectives on the data. This feature of the model provides perspectives on aim 2 and the relative importance of paths g–l in Fig. 1. To ascertain perspectives of the effects of clinic-level variables on provider variables, random intercept MSEM with the provider-level variables can be estimated as a function of the clinic variables that include dummy coded treatment variables (4Rs and 2Ss MFG + CIT versus 4Rs and 2Ss MFG) impacting the clinic mediators of readiness, leadership support, and climate, which in turn, affect the provider-level intercepts. This modeling, or variants of it, address aims 3 and 4.

The overall analytic structure requires strategic use of different dummy contrasts and limited information estimation of various MSEM models that map onto the questions dictated by the aims, coupled with judicious use of mediational tests linked to joint significance testing. An alternative analytic structure is to work with all four time periods simultaneously in a classic growth curve model and then to model the linear growth in variables as a function of the provider and clinic variables in strategically defined limited information estimation frameworks dictated by the overall model structure in Fig. 2. We also will explore this approach. Analyses of variable importance (Fig. 1) have been summarized by Tonidandel et al. [58]. Of the two major tools to address the issue (dominance analysis and relative weight analysis), we will use relative weight analysis to gain perspectives because of the less intense computational demands that it makes and its overall flexibility. Missing data will be treated using Full Information Maximum Likelihood (FIML) methods.

A Data Monitoring and Review Board is responsible for reviewing this study’s data to ensure quality and integrity, the safety of participants and study progress, and to make any determinations regarding potential changes to the study. This is comprised of the investigative team with ongoing support from New York University’s Institutional Review Board (IRB). The DMRB meets on a quarterly basis under normal circumstances, or within two business days should an adverse event occur. This process is independent from the sponsors, although they will be notified in the case of a significant change to study protocol or in the case of an adverse event.

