**Methods/design:**

This study, a Hybrid Type II effectiveness-implementation research trial, blends clinical effectiveness and implementation research methods to examine the impact of the 4Rs and 2Ss Multiple Family Group (MFG) intervention, family level mediators of child outcomes, clinic/provider-level mediators of implementation, and the impact of CITs on uptake and long-term utilization of this model. All New York City public outpatient mental health clinics have been invited to participate. A sampling procedure that included randomization at the agency level and a sub-study to examine the impact of clinic choice upon outcomes yielded a distribution of clinics across three study conditions. Quantitative data measuring child outcomes, organizational factors and implementation fidelity will be collected from caregivers and providers at baseline, 8, and 16 weeks from baseline, and 6 months from treatment completion. The expected participation is 134 clinics, 268 providers, and 2688 caregiver/child dyads. We will use mediation analysis with a multi-level Structural Equation Modeling (SEM) (MSEM including family level variables, provider variables, and clinic variables), as well as mediation tests to examine study hypotheses.

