### Hypotheses and data analytic strategy

The purpose of this study is to examine outcomes associated with the 4Rs and 2Ss MFG, implementation processes that impact uptake and sustained use of the intervention over time, and the impact of an innovative change agent team upon outcomes. The following hypotheses will be tested:
*Aim #1*: to examine the short-term and longitudinal impact of 4Rs and 2Ss MFG on child ODD and functioning
*Hypothesis #1*: youth who participate in 4Rs and 2Ss MFG will display significantly reduced conduct difficulties and increased functioning over time compared to those involved in standard care: youth in the 4Rs and 2Ss MFG + CIT condition will evidence the greatest magnitude of change in outcomes over time
*Aim #2*: to examine family level mediators (e.g., parenting, family process) of child outcomes
*Hypothesis #1*: based on existing 4Rs and 2Ss MFG findings, specific family level variables (caregiver stress, the parent/child relationship and established rules) will be associated with significantly greater impact on child outcomes over time relative to social support, established responsibilities, and respectful communication
*Aim #3*: to examine clinic- (readiness to adopt an innovation, leadership support, and climate) and provider-level moderators (engagement, preparedness, motivation) of 4Rs and 2Ss MFG implementation and integration
*Hypothesis #1*: leadership support will evidence significantly greater impact on 4Rs and 2Ss MFG implementation/integration in comparison to general readiness and clinic climate
*Hypothesis #2*: provider motivation will evidence significantly greater impact on 4Rs and 2Ss MFG implementation/integration relative to other provider-level variables
*Aim #4*: to examine the impact of CITs on clinic- and provider-level moderators of 4Rs and 2Ss MFG implementation and integration
*Hypothesis #1*: clinic directors assigned to MFG + CIT will evidence significantly higher readiness for innovation and support, and providers assigned to MFG + CIT will evidence significantly higher preparedness and motivation to implement MFG relative to MFG alone
*Hypothesis #2*: preparedness, motivation of providers, and leadership support assigned to MFG + CIT will be maintained over time and be significantly higher relative to MFG alone
*Hypothesis #3*: providers assigned to MFG + CIT will evidence significantly enhanced fidelity to MFG relative to MFG only

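### The model outlined for Aim 4 Hypotheses 1 and 2 names no baseline value of the clinic and provider variables it compares, although organizational factors are measured at baseline and some agencies choose their arm

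*Protocol article*

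**What the plan says.** The Analytic strategy section of the protocol article outlines two pieces of modelling.

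- **Child outcomes (level 1).** Post-test outcomes are modelled on family predictors "using baseline measures of outcomes and family mediators as covariates". The adjustment set is named.
- **Aims 3 and 4.** Here "random intercept MSEM with the provider-level variables can be estimated as a function of the clinic variables that include dummy coded treatment variables". The dummy contrasts MFG + CIT with MFG and is described as "impacting the clinic mediators of readiness, leadership support, and climate, which in turn, affect the provider-level intercepts". No baseline value of any clinic or provider variable is mentioned. The outline closes: "This modeling, or variants of it, address aims 3 and 4".

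Two other models in the section involve repeated measures. In the panel model, "The follow-up (6-month) measures of the mediators and the outcomes are included within the model in a classic SEM panel model with autoregressive effects"; this ties the 6-month data to the immediate post-test data. Later, "An alternative analytic structure is to work with all four time periods simultaneously in a classic growth curve model", which the authors say they will also explore.

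The Abstract (Methods/design) states that "organizational factors and implementation fidelity will be collected from caregivers and providers at baseline, 8, and 16 weeks from baseline", so baseline organizational data are planned. Under Aim 4, Hypothesis 1 expects higher readiness and support among clinic directors, and that "providers assigned to MFG + CIT will evidence significantly higher preparedness and motivation to implement MFG relative to MFG alone". Hypothesis 2 expects the advantage to persist over time.

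Under Sampling procedure, single-site agencies and agencies with two to four clinics are randomized, with all clinics of one agency sharing a condition. Agencies with five or more clinics select their own condition.

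**The concern.** Readiness, leadership support, climate and provider motivation exist in a clinic before any CIT meeting, and clinics will differ in them. A comparison of follow-up values that ignores the starting values has two weaknesses.

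1. **Precision.** The between-clinic variation that baseline would explain stays in the error term. Aim 4 uses only two of the three arms and is carried by clinics, or more strictly by agencies, so this is where the trial has few units.
2. **Self-selection.** An agency that chooses the arm with extra implementation meetings may already be readier or better led. Without baseline adjustment, part of that prior difference is counted as an effect of the CIT.

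Both weaknesses affect the direct tests in Hypotheses 1 and 2. They also affect the first two links of the proposed mediation chain (paths m and n, described under Purpose of this study).

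**Working it through.** **Inputs from the article (Participants).** The master list has 168 clinics and about 80% are expected to take part: 0.80 × 168 = 134.4, stated as 134. Two providers per clinic gives 134 × 2 = 268, as stated. The planned counts therefore reproduce. Split evenly over three arms, 134 / 3 = 44.7, or about 45 clinics per arm.

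**Inputs not in the article (assumptions).** The article gives no effect size, alpha, or baseline-to-follow-up correlation for Aim 4. I assume two-sided alpha 0.05, a standardized effect d = 0.5, and correlation ρ of 0.3, 0.5 or 0.7. I also treat clinics as independent.

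**Precision.** Adjusting for baseline multiplies residual variance by 1 − ρ², so the effective effect is d / √(1 − ρ²). The noncentrality is that value × √(45/2). Power is from the noncentral t, with 88 degrees of freedom unadjusted and 87 adjusted.

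| ρ | 1 − ρ² | effective d | noncentrality | power |
|---|---|---|---|---|
| unadjusted | 1.00 | 0.500 | 2.37 | 65.0% |
| 0.3 | 0.91 | 0.524 | 2.49 | 69.1% |
| 0.5 | 0.75 | 0.577 | 2.74 | 77.3% |
| 0.7 | 0.51 | 0.700 | 3.32 | 90.7% |

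The gain is about 4, 12 and 26 percentage points. A separate calculation with 44.7 clinics per arm gives 65.7%, 69.7%, 77.9% and 91.1%, within one point of the table. By that calculation, the clinics per arm needed for 80% power at d = 0.5 are 63 unadjusted and 58, 48 or 33 adjusted.

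**Carry-over of a baseline difference.** If the arms differ at baseline by D (in SDs), the expected contribution to an unadjusted follow-up contrast is ρ × D. For an assumed D = 0.3, that is 0.3 × 0.3 = 0.09 SD up to 0.7 × 0.3 = 0.21 SD. Against a true effect of 0.5 SD this matters.

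**Chance and self-selection.** Between two randomized arms of 45 independent clinics, the baseline difference has SD √(2/45) = 0.21. That is random variation already reflected in the standard error: it costs precision but does not bias the contrast. Bias can come from the agencies that choose their arm, because D need not average zero among them. The article does not give their number, so the size of that bias cannot be computed.

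**Do the other models supply the baseline?** The panel model links 6-month values to post-test values and names no baseline for clinic or provider variables. The growth model would use the baseline wave, but it is an alternative to be explored. It is also described as modelling growth as a function of provider and clinic variables, so it does not clearly adjust those variables for their own starting values.

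**The case against.** The strongest reply is that a condensed article has been silent, not wrong. The wording is permissive (the model "can be" estimated in the stated way, and variants are allowed), and no wave is given for the clinic and provider variables. The authors call Fig. 2 their primary reference, and it is not visible here. The section on hypotheses also says Aims 3 and 4 look at readiness and motivation initially and over time. A fuller plan may list the covariates.

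Much of this stands, and it rules out three stronger readings that a reader might infer.

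- *That the plan specifies a regression excluding baseline.* It does not. It names baseline covariates for one model and none for the other.
- *That the fault runs through all of Aims 3 and 4.* Aim 3 compares the importance of predictors and has no MFG + CIT contrast. Aim 4 Hypotheses 3 and 4 concern fidelity and groups initiated and completed, which have no pre-intervention value.
- *That chance imbalance between randomized clinics biases the CIT effect.* It does not, as shown in the working.

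The power figures are also open to challenge. They rest on assumed inputs, and at ρ = 0.3 the gain is only about 4 points. Clinics of one agency share a condition, so fewer than 45 independent units per arm carry the contrast.

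What the reply does not remove is the asymmetry within one section. Covariates were not left generally to another document: they were stated for level 1 and are absent from the outline said to address Aim 4. Allowing variants is not the same as fixing the adjustment in advance. A post-assignment reading is also the natural one for Hypotheses 1 and 2, which claim that the CIT changes these variables.

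**Conclusion.** The concern holds in a limited form, for Aim 4 Hypotheses 1 and 2 and paths m and n. The outlined model names no baseline value of the clinic mediators or provider variables, although organizational factors are collected at baseline and level 1 already adjusts.

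Fitted as outlined, it loses precision: about 4 to 26 points of power under the assumptions above. The absolute power levels will be lower than tabulated because agencies, not clinics, are the assigned units for multi-site agencies. It also leaves the contrast open to pre-existing differences among agencies that chose their arm. The direction of that bias is plausible, but its size cannot be derived from the article.

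The primary outcomes belong to Aims 1 and 2, and the article calls the CIT test a secondary objective. This is therefore a change worth making, not one on which the trial's main result depends.

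**What to change.** Add a sentence to the Analytic strategy: in the Aim 4 Hypothesis 1 and 2 equations, the baseline value of each clinic mediator (readiness, leadership support, climate) and of each provider variable (preparedness, motivation) enters as a covariate for its own follow-up value, as level 1 already does.

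State that only baseline records completed before the clinic's MFG training or CIT adaptation meetings count. Trial status reports that some clinics had already had these, and a later record could contain part of the effect being tested.

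The cost is a few more parameters and no new data collection. Some clinics may lack a pre-contact record; the article does not say how many. Those gaps can be handled by the planned FIML, provided the baseline variables are part of the model and the missing-at-random assumption is reasonable. Adjustment will reduce confounding from arm choice only as far as the measured baseline captures it.

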*Hypothesis #4*: clinics assigned to MFG + CIT will have more MFGs initiated and completed (with high fidelity and attendance) relative to MFG alone

Overall, the two primary outcomes being tested in this study are changes in child behavior and child functioning. These outcomes are being tested specifically in aims 1 and 2, as measured by the Disruptive Behavior Disorders Rating Scale Oppositional Defiant Subscale [38], Iowa Conners Rating Scale-Oppositional/Defiant Subscale [40] and the Impairment Rating Scale (IRS) [41]. Aims 3 and 4 intend to measure mediators of the primary outcome, by testing clinic readiness and motivation to implement the 4Rs and 2Ss intervention initially and over time, and testing whether fidelity has been adhered to.

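### The growth model fits one straight line across treatment and follow-up, so it cannot separate the short-term from the longitudinal effect that Aim 1 asks for

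*Protocol article*

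**What the plan says.** Under Hypotheses and data analytic strategy, Aim 1 is "to examine the short-term and longitudinal impact of 4Rs and 2Ss MFG on child ODD and functioning", and its hypothesis is that children in the group programme "will display significantly reduced conduct difficulties and increased functioning over time compared to those involved in standard care". The same section states that "the two primary outcomes being tested in this study are changes in child behavior and child functioning".

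The Analytic strategy section (text after Fig. 2) describes two models that involve child outcomes.

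- **Panel model.** In this multilevel SEM "child outcomes at the immediate post test are modeled as a function of the family predictors", "using baseline measures of outcomes and family mediators as covariates". The 6-month mediators and outcomes are "included within the model in a classic SEM panel model with autoregressive effects". The text ties this model to Aim 2 and names baseline, post-test and 6-month data; it does not mention the 8-week visit.
- **Growth model.** The alternative is to "work with all four time periods simultaneously in a classic growth curve model and then to model the linear growth in variables", with that growth explained by provider and clinic variables. The team says that it will also explore this approach.

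The Abstract places the visits at baseline, 8 weeks, 16 weeks and 6 months after treatment completion. The description of the conditions gives the group programme a length of 16 weeks.

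**The concern.** A linear growth model assumes that the difference between arms changes at the same weekly rate throughout. Here treatment is delivered for 16 weeks and is followed by about 26 weeks without it. If the benefit builds during the groups and then holds or fades, the true path bends at week 16 and a single slope averages two different phases. Aim 1 names both a short-term and a longitudinal effect, and one slope supplies one number for the two.

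The gain during treatment could therefore be reported as much smaller than it was. If the model also lets the arms differ at baseline, part of the gain would appear as a baseline difference that does not exist. With fade-out, the slope can approach zero or change sign although the programme worked while it ran.

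A related caution applies to the panel model. The family variables measured after baseline are what the programme is meant to change. An arm coefficient estimated with them held fixed is a direct effect, not the effect in Hypothesis 1.

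**Working it through.** **Inputs.** Visits at t = 0, 8, 16 and 42 weeks (Abstract; 42 = 16 + 26, taking 6 months as 26 weeks); treatment length 16 weeks. The article states no effect size or effect shape, so there is no figure of its own to reproduce. I assume an arm difference that rises linearly to 0.50 SD at week 16 and is then held, halved or lost by the last visit.

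**Slope by least squares.** The mean of t is 66/4 = 16.5 and the deviations are −16.5, −8.5, −0.5 and 25.5. The sum of squares is 272.25 + 72.25 + 0.25 + 650.25 = 995. Each visit's weight in the slope is its deviation divided by 995: −0.0166, −0.0085, −0.0005 and +0.0256. The end-of-treatment visit has almost no weight in the slope.

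*Held*, differences 0, 0.25, 0.50, 0.50:
- slope = (−8.5×0.25 − 0.5×0.50 + 25.5×0.50)/995 = 10.375/995 = 0.01043 per week
- implied gain over weeks 0 to 16 = 16 × 0.01043 = 0.17 SD, against a true 0.50
- intercept = 0.3125 − 16.5 × 0.01043 = 0.14 SD, a baseline difference that is not there
- fitted difference at week 16 = 0.14 + 0.17 = 0.31 SD

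*Halved*, last value 0.25: slope = 4.0/995, gain = 0.06 SD.

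*Lost*, last value 0: slope = −2.375/995, gain = −0.04 SD.

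**Other ways to fit the line.**
- Baseline difference fixed at zero: slope = Σtd/Σt², with Σt² = 64 + 256 + 1764 = 2084. Held: 31/2084 × 16 = 0.24. Halved: 20.5/2084 × 16 = 0.16. Lost: 10/2084 × 16 = 0.08.
- Visits coded 0, 1, 2, 3 (sum of squares 5; week 16 is two steps). Held: 0.875/5 × 2 = 0.35. Halved: 0.5/5 × 2 = 0.20. Lost: 0.125/5 × 2 = 0.05.
- Both together (Σt² = 14). Held: 2.75/14 × 2 = 0.39. Halved: 2.0/14 × 2 = 0.29. Lost: 1.25/14 × 2 = 0.18.
- Last visit at week 26, should 6 months be counted from baseline (sum of squares 371). Held: 7.375/371 × 16 = 0.32. Halved: 4.0/371 × 16 = 0.17. Lost: 0.625/371 × 16 = 0.03.

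| Implied 0–16 week gain (true value 0.50 SD) | Held | Halved | Lost |
|---|---|---|---|
| Weeks 0/8/16/42, free baseline | 0.17 | 0.06 | −0.04 |
| Same, baseline difference zero | 0.24 | 0.16 | 0.08 |
| Visits coded 0–3, free baseline | 0.35 | 0.20 | 0.05 |
| Visits coded 0–3, baseline difference zero | 0.39 | 0.29 | 0.18 |
| Weeks 0/8/16/26, free baseline | 0.32 | 0.17 | 0.03 |

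With generalised least squares and a correlation of 0.7 between successive visits (first-order autoregressive), the first row becomes 0.11 (held) and −0.01 (halved). The line returns 0.50 only if the benefit keeps growing at the same rate after the groups stop, or at the same step per visit under the 0–3 coding.

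**Panel model.** Take an assumed total effect of −0.40. With the mediator held fixed, the arm coefficient is −0.40 × (1 − proportion mediated): −0.30, −0.20 and −0.10 for 25%, 50% and 75% mediated. In a large simulation of a path model with arm paths to both mediator and outcome, direct plus indirect returned −0.40 each time to within simulation error, including cases with mediator–outcome confounding. The total effect is therefore recoverable if it is computed as that sum.

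**The case against.** A reader might infer that no stated model can estimate Hypothesis 1, because the child-outcome model conditions on post-randomisation mediators and standard care is left out of the treatment coding. The documents do not support this.

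- In a mediation SEM the family variables are themselves outcomes of treatment, and direct plus indirect gives the total effect. The covariates that the text names are baseline measures. Nothing says that the direct path alone will be reported as the answer to Hypothesis 1.
- The coding "dummy coded treatment variables (4Rs and 2Ss MFG + CIT versus 4Rs and 2Ss MFG" stands in the sentences on clinic and provider variables, which serve Aims 3 and 4. All Aim 4 hypotheses compare those two arms, so the coding is right there and does not exclude standard care elsewhere. The text goes on to promise different contrasts matched to the aims.
- Fig. 2, which the article makes its main reference for the models, is not available, so the treatment paths to child outcomes cannot be judged. That the prose ties no model to Aim 1 is mainly missing detail in a condensed article.

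Against the growth-model point itself, the model is only an alternative to be explored, and a slope difference does bear on change over time as Hypothesis 1 words it. The effect shape, time coding and baseline handling are all assumptions. This limits the weight of the point and is why a range is shown. It does not remove the point: linear growth over all four visits is a stated choice, and in every variant computed the implied gain during treatment falls short when the benefit plateaus or fades.

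**Conclusion.** The point stands for the growth model. A single linear slope over weeks 0, 8, 16 and about 42 cannot separate the short-term from the longitudinal impact unless the benefit keeps accruing after treatment at the same rate. For an assumed 0.50 SD benefit at week 16 that is maintained, the line implies a gain during treatment of 0.17 SD. That becomes 0.24 SD with no baseline difference allowed, 0.35 SD with visits coded 0 to 3, and 0.39 SD with both. If half the benefit fades, the same four figures are 0.06, 0.16, 0.20 and 0.29 SD. They show direction and rough size and are not predictions for this trial.

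For the panel model only a caution remains: an arm coefficient with the family mediators held fixed should not be read as the Hypothesis 1 effect. Because the growth model is an exploratory alternative, this is a worthwhile correction to the analysis text, not a flaw that invalidates the plan.

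**What to change.** For the child outcomes under Aim 1, replace the single linear slope with one of two forms:

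- arm by categorical visit (8 weeks, 16 weeks, 6 months); or
- a piecewise slope with a knot at week 16.

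In either form, adjust for the baseline value of the outcome, account for clustering, and include all three arms. State the contrasts of the group programme with standard care, and of the programme plus implementation team with standard care. Include no family or provider variable measured after baseline. Report the 16-week contrast as the short-term effect and the 6-month contrast as the longitudinal effect.

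Keep the multilevel SEM for Aims 2 to 4. If a total effect is quoted from it, say that it is the sum of direct and indirect effects.

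The cost is a change of analysis wording and, relative to a single slope difference, one extra parameter per arm contrast with the knot or two with categorical visit. No visit, measure or sample size changes.

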## Background

Oppositional defiant disorder (ODD) is a chronic and impairing mental health disorder that afflicts between 1 and 21% of the population, and primarily elementary school-age children, with the median age of onset being 11.6 years [1]. Along with conduct disorder and attention deficit hyperactivity disorder, ODD is part of the disruptive behavior disorder (DBD) diagnostic group, which is characterized by severe behavioral problems including impulsivity, aggression, violence, delinquency, and criminal acts [1].

Family poverty is one of the greatest risk factors for the onset and perpetuation of DBDs [2–4]: studies indicate that the accumulation of risk factors associated with poverty, including increased exposure to violence and traumatic events, devastating impact of substance abuse, criminal activity, and chronic disease, as well as family strain have an additive effect, in that the more risk factors a child is exposed to increases their likelihood of exhibiting serious behavioral challenges [1, 5]. Accordingly, children living in poverty experience DBDs at rates of up to four times higher than children reared in families with more financial resources [6].

Treatments for DBDs are among the most well-studied and efficacious [7], yet as many as 80% of children in poverty-impacted communities do not receive services. And for those who do manage to initially engage in behavioral health care, premature attrition from services approaches 50% [1, 8]. Further, the uptake of evidence-based practices (EBPs) in community-based settings is slow and beset with challenges. An oft-cited statistic suggests that it can take as long as two decades before treatments that are studied in research trials become integrated as part of standard practice in real-world settings [9] if at all. Thus, even though children who live in poor communities are at the highest risk for DBDs, they are the least likely to receive effective mental health services.

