### Description of the conditions

The study consists of three arms: two active treatment and one comparison condition:The 4Rs and 2Ss Multiple Family Group interventionThe 4Rs and 2Ss MFG is a 16-week group for urban children of between 7 and 11 years of age with ODD and their caregiver(s). In this model, six to eight families meet in weekly sessions focused on addressing family and parenting factors associated with behavior problems [30–33]. Session content also addresses lack of social support and high stress, which are two factors known to hinder treatment attendance [34–36]. Families are provided with free childcare, transportation expenses, and a meal to address common logistical barriers to attendance [8]. Moreover, perceptual barriers, such as stigma and fears of being blamed for their child’s difficulties, are targeted through group processes which normalize family difficulties, validate their expertise in solving problems, and promote mutual aid [37]. Providers who participate in this condition will attend a 5-h training to learn the 4Rs and 2Ss MFG model; thereafter, they will participate in bimonthly supervision over the course of implementationThe 4Rs and 2Ss MFG + CITIn addition to implementing the model and receiving supervision, a CIT consisting of providers, a clinic director and supervisor will participate in ongoing meetings with the research team’s adaptation specialist for a guided analysis of the structure, content and processes of the treatment model, including those that are amenable to modification and those that must remain unchanged in order to maintain fidelityStandard careStandard care includes the services that the clinic normally provides to children with behavioral problems, including outpatient mental health therapy and pharmacology

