### Measures

Data collection will occur at baseline, 8, and 16 weeks from baseline, and at 6-month follow-up. Demographic characteristics about familial factors (e.g., age, race/ethnicity, family income) will be collected via a questionnaire used in prior studies. A separate demographic questionnaire will be administered to providers to gather information including their age, race/ethnicity, education, and credentials.

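### The child-outcome model as described leaves week-8 scores outside the FIML likelihood, so the MFG versus standard-care contrast is exposed to bias if loss after week 8 depends on interim symptoms

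*Protocol article*

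**What the plan says.** The Measures section sets four assessments: "Data collection will occur at baseline, 8, and 16 weeks from baseline, and at 6-month follow-up".

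The Analytic strategy section describes one child-outcome model in detail. Child outcomes at the immediate post test are regressed on family predictors, "using baseline measures of outcomes and family mediators as covariates, taking into account the clustering at the higher levels of the model". The later wave is then attached: "The follow-up (6-month) measures of the mediators and the outcomes are included within the model in a classic SEM panel model with autoregressive effects". Week-8 outcome scores are not named in this model.

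Week 8 enters in the next paragraph: "An alternative analytic structure is to work with all four time periods simultaneously in a classic growth curve model". The article says only that this approach will also be explored.

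Missing data get one sentence: "Missing data will be treated using Full Information Maximum Likelihood (FIML) methods". No auxiliary variables are named.

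The Ethical issues section adds that if a child's symptoms worsen, study participation will be halted and care provided under clinic procedure.

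**The concern.** FIML gives valid estimates when missingness is random given the variables inside the fitted likelihood. In the described model those are baseline, post-test and 6-month measures plus the family predictors. Suppose a family is assessed at week 8 and then permanently lost. On the outcome side it contributes its baseline score only, although a later and more informative score was collected. The model then predicts that child's post-test from baseline, as if nothing were known of the course on treatment.

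This is harmless if loss after week 8 has nothing to do with how the child was doing at week 8, once baseline and arm are known. The halting provision is a documented route by which it could. At stake is the Aim 1 contrast on ODD symptoms and impairment. If children doing badly leave standard care more than they leave MFG, the benefit is understated. If the selection runs the other way, it is overstated.

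**Working it through.** **Plan figures.** The article gives no dropout rate, effect size, SD or wave correlation, so it has no figure on this point to reproduce. Its one sample-size figure does reproduce (168 clinics × 0.80 × 20 dyads = 2688; 2688 / 3 = 896 per arm), but it does not matter here, because this bias does not shrink with n.

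**Assumed inputs** (none from the article):
- Outcome SD 1; higher score is worse.
- True effect -0.15 at week 8 and -0.30 at week 16.
- Correlations for baseline to week 8, week 8 to week 16, and baseline to week 16: set A 0.50, 0.70, 0.45; set B 0.60, 0.60, 0.50.
- Permanent loss after week 8; no clustering; 500,000 children per arm.

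**Estimators.** With baseline complete and permanent loss, FIML reduces to regressions.
- Without week 8: Y16 on arm and Y0 among children seen at week 16. The estimate is the arm coefficient.
- With week 8: Y16 on arm, Y0 and Y8 among those seen at week 16 (coefficients c_arm, c_8), and Y8 on arm and Y0 in everyone (coefficient e_arm). The estimate is c_arm + c_8 × e_arm.

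**Why bias arises.** Approximately, bias = b × (difference between arms in the mean baseline-adjusted week-8 score of those retained). Here b is the slope of week 16 on week 8 given baseline: (0.70 - 0.45 × 0.50) / (1 - 0.50²) = 0.475 / 0.75 = 0.63 in set A, and (0.60 - 0.50 × 0.60) / (1 - 0.60²) = 0.30 / 0.64 = 0.47 in set B. If selection shifts both arms equally, the difference is zero and the contrast is unbiased.

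**Results without week 8** (truth -0.30; loss shown as standard care / MFG; relative bias = 1 - estimate / -0.30):

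| Loss | Depends on | Set A | Set B | Bias |
|---|---|---|---|---|
| 40 / 15% | arm only | -0.302 | -0.299 | none |
| 40 / 15% | baseline, slopes differ by arm | -0.297 | -0.303 | none |
| 25 / 25% | week 8, same slope in both arms | -0.304 | -0.298 | none visible |
| 30 / 20% | week 8, log-odds 0.5 per SD, both arms | -0.277 | -0.285 | 5-8% too small |
| 40 / 15% | week 8, log-odds 1 per SD, both arms | -0.204 | -0.240 | 20-32% too small |
| 25 / 25% | week 8 in standard care only, log-odds 1 | -0.197 | -0.232 | 23-34% too small |
| 40 / 15% | week 8 in standard care only, log-odds 1 | -0.139 | -0.197 | 34-54% too small |
| 40 / 15% | week 8 in MFG only, log-odds 1 | -0.364 | -0.343 | 14-21% too large |

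With week 8 in the likelihood, every scenario returned -0.297 to -0.305.

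**Second set of assumptions.** With set A and dropout odds changing 2-fold per SD of the week-8 score in both arms, the bias without week 8 is 14-15% at 30 / 15% loss, 20-21% at 40 / 20% and 31% at 50 / 20%. The sign depends on whether worse or improved children leave.

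**Adding the 6-month wave.** The described model includes that wave. Suppose half of those missing at week 16 are seen at 6 months, with assumed 6-month correlations of 0.40 with baseline and 0.70 with week 16. At 2-fold odds the bias then falls to about 11%, 14% and 19% for the same three pairs of loss rates.

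**The case against.** **A reader might infer that unequal dropout between arms is itself the problem.** It is not: the first two rows of the table show no bias at 40% versus 15%. Nor are equal rates safe, as the 25 / 25% row with dependence in one arm shows. What matters is dependence on week-8 status beyond baseline and arm, together with rates or mechanisms that differ by arm.

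**A reader might infer that the article forecasts informative, arm-unequal loss.** It does not. The Background figure ("premature attrition from services approaches 50"%) is attrition from services among children in poverty, not loss from trial assessments, and is not given by arm. The MFG support ("Families are provided with free childcare, transportation expenses, and a meal to address common logistical barriers to attendance") concerns attendance at group sessions. Both make unequal loss conceivable, but neither predicts it.

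**A reader might call the described panel the main Aim 1 model.** That is an inference. The text links the level-1 model to Aim 2, and the only treatment dummy it names is MFG + CIT versus MFG. The Aim 1 contrast is not written out separately, and Hypothesis 1, about change over time, would suit the four-wave model. Against this, the section presents the MSEM as the framework for testing all the aims, the primary outcomes belong to Aims 1 and 2, and the four-wave model carries no commitment.

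**Fig. 2 is not shown.** The text does not say at which wave the family predictors are measured. Week-8 mediators in the model would recover some information, though they would not replace the week-8 outcome.

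**Auxiliary variables are usually left to the analysis plan.** True, and silence about them alone would not be a finding. Here, however, the article states both which waves are in the model and how missing data are handled. The weakness lies in that stated combination.

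**Conclusion.** The concern holds in a limited form. FIML on the child-outcome model as described leaves collected week-8 outcomes unused and so rests on a stronger missing-at-random assumption than the data require. The halting provision gives a concrete reason to doubt that assumption, although the article does not say whether assessments also stop when participation is halted.

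Under the assumptions above, with permanent loss, the bias is about 5-8% of a 0.30 SD effect in mild cases and about 15-30% in stronger ones. It is larger in some one-arm scenarios and smaller if families lost at week 16 return at 6 months. The direction can go either way. No rate in the article says which case applies, so these sizes show what is possible, not what to expect. The conclusion also assumes that the described panel, rather than the four-wave alternative, carries the arm comparison.

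**What to change.** In the Analytic strategy section, state that the week-8 DBD-ODD, IOWA and IRS scores will enter the FIML likelihood of every child-outcome model used for the arm comparison. They can be a modelled wave or saturated-correlates auxiliary variables. As auxiliary variables they leave the structural paths and the estimand unchanged.

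The cost is one sentence and a few more covariances to estimate. No new data are needed, since week 8 is already collected. The small downside is a somewhat larger three-level model to fit. The change does not protect against loss that depends on unobserved change after week 8.
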